**Fig 4 pone.0270766.g004:**
[figure not shown]
Timeline of outcome measurement. FSS: Fatigue Severity Scale; 6MWT: 6 Meters Walk Test; STST; Sit-To-Stand Test; ACT: Arm Curl Test; PCFS: Post-Covid Functional Scale; GSES: General Self Efficacy Scale; DASS: Depression, Anxiety and Stress Scale; BRSQ: Behavioral Regulation in Sport Questionnaire; MSPSS: Multidimensional Scale of Perceived Social Support.

#### Sample size calculation

A sample size of 50 subjects will be required, 20 in each group, plus 10 in anticipation of future losses according to the recommendations for RCT pilot studies [95, 96].

#### Data management

A detailed database will be set up to track each participant’s progress, including all evaluations. All the generated data will be recorded and stored on password-protected computers, that will be only accessible to the researchers involved in this study. An independent researcher will monitor data collection progress and safety. Data will be analyzed when all recruitment and data collection has been performed.

#### Statistical analysis

Statistical analysis will be performed with Statistical Package for the Social Sciences version 25.0 (SPSS Inc, Chicago, IL). The significance level will be 0.05 for all statistical analyses. Descriptive statistics, including frequency counts for categorical variables and measurements of central tendency and dispersion for continuous variables (standard deviation, 95% confidence interval) will be calculated to summarize the data.

The Shapiro-Wilk test will be used to determine the normality of the data.

General lineal models will be performed to compare the intervention effects [time (pre-intervention vs post-intervention vs follow-up 1 and 2 assessments) x group interaction] on the primary and secondary outcomes: severity of fatigue, functional status, self-efficacy, depression, anxiety and stress, quality of live, behavioral regulation in sport and perceived social support. It will be examined with analysis of variance (ANOVA) mixed model for repeated measures when normal distribution will be detected. A post hoc test will be used to locate the differences between the groups, if necessary. If data are not normally distributed, statistical analysis will be performed using non-parametric correspondent tests like Friedman test to compare the three moments involved and Wilcoxon test if statistics significance will be reached in previous Friedman test. In Wilcoxon test, type I error will be divided by the number of tests done.

For the aerobic capacity, strength, functional status post-COVID and feasibility outcomes, comparisons between-groups outcomes will be using t-tests for independent samples and Levene test for parametric data, or Mann-Whitney test U tests for non-parametric data. Chi-square and Fisher tests will be used of independence for categorical data. Finally, in the event of possible dropouts, analyses will be conducted as intention to treat.

Between- and within-group effect sizes using Cohen’s d or r for main outcomes will also be computed.

Chi square test for qualitative data and t-test or Mann-Whitney for normal or not normal data respectively will be used to check the comparability between the two groups at baseline.

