### Procedure

At the time of hospital discharge all potential participants will receive the study information with a telephone number to contact. Those who agree to participate will call to the information number provided in the information sheet. One of the researchers of the study will ensure that the patient meets the inclusion and exclusion criteria and will schedule the patient for the baseline and pre-intervention assessment. In the first meeting with the researcher, the patient will be asked to sign the informed consent form.

All assessments will be always performed at the same time and place in the hospital to maximally preserve the participant conditions. Each assessment will last about 60 min. This evaluation shall be carried out according to the same procedure previously trained.

Once the baseline and pre-intervention evaluation is completed, a second researcher will assign each patient to the ATG or BRG according to the 1:1 randomization previously done with a web page (www.randomizer.org). This same researcher will help the ATG patients to install the telerehabilitation platform in the mobile (through an app) or will explain the home booklet-based program to the BRG patients. The intervention will be prescribed considering the starting level of the program which will depend on the pre-intervention FSS score.

Every two weeks during the intervention, all patients will receive a control call from the second researcher to ask them about possible incidents and decide if the patient must progress to the next exercise phase based on the intensity of fatigue perceived by each patient. Three- and six- months after the intervention, patients will receive a follow-up call to analyze the level of fatigue (FSS), the functional status (PCFS), the quality of life (SF-12) and the psychosocial factors (GSES-12, DASS-21, BRSQ-36, MSPSS) (Figs 1 and 2).

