### Outcome measures

#### Primary outcome: Fatigue

The primary outcome measure will be the fatigue, measured with the Fatigue Severity Scale (FSS). The FSS is a self-reported scale that allows assessing the severity of fatigue as a sense of physical tiredness, muscle weakness and lack of energy [38–40]. It is composed of 9 items with scores ranging from 1 = strongly disagree to 7 = strongly agree. The higher the number, the greater the severity of fatigue. The most common cut-off point is a mean score of 4 point, considering equal or more than 4 as severe fatigue [38, 41–45]. Three levels of severity will be considered: 4 = borderline fatigue; 5 = high fatigue; 6–7 = very high fatigue [44]. It has been shown to be reliable [38].

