All the clinical outcomes (FSS, PCFS, GSES-12, DASS-21, BRSQ-36, MSPSS, SF-12) will be measured at pre-intervention, post-intervention and at three- and six-months follow-up. The functional status outcomes (6MWT, 30” ACT and 30” STST) only will be measured pre- and post-intervention. Regarding the feasibility outcomes, incidences and adherence will be collected during the control calls every two weeks. Satisfaction will be measured in the post-intervention evaluation. The timeline is shown in Fig 4.

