## Discussion

This protocol describes a pilot and feasibility study to analyze the efficacy of an exercise and education therapeutic program using asynchronous telerehabilitation for post-COVID-19 patients. The aim of the pilot study will be to analyze if there are improvements in the participants´ level of fatigue and if these changes are maintained in the short (3 months) and medium term (6 months) and compare it with traditional home rehabilitation using a booklet. The secondary aim will be to analyze the feasibility of this pilot study.

Telerehabilitation is well accepted in terms of overall user experience, adherence, and satisfaction [94]. So, it represents a great opportunity for the treatment and monitoring of long-term patients. Currently, the large increase of COVID-19 cases during 2020 and 2021 has made telerehabilitation-based consultation a viable and reliable option in several pathologies. Scientific evidence shows how telerehabilitation is already effective in post-COVID-19 patients, as reported in the systematic review of da Silva et al. [97] where it was found that a physical programme using telerehabilitation can improve functional capacity, dyspnea and quality of life. Similarly, Dalbosco-Salas et al. [98], found that a group of post-COVID-19 patients undergo remote rehabilitation using synchronous telerehabilitation, achieved improvements in physical condition and quality of life. Although their model is on-line and there is no control group, the study shows positive results for post-COVID-19 patients in lower limb strength and quality of life. Furthermore, in most of the studies carried out in the acute and post-COVID-19 patients, the control group does not receive treatment.

Moreover, telerehabilitation has also shown to be effective in many other different conditions such as musculoskeletal pain, chronic obstructive pulmonary disease (COPD) or cardiovascular disease [99]. The study of Lewis et al. [100] showed that telerehabilitation is effective in COPD patients on multiple variables such as lower limb strength, fatigue, dyspnea, and anxiety, including improvements also in patient engagement and exercise progression. Similar results were obtained by Batalik et al. [101], who performed a study with asynchronous telerehabilitation in cardiac patients and showed also to be effective to improve the aerobic capacity assessed with the 200 meter fast-walk test.

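### The FSS treatment effect is fixed as a four-visit omnibus time-by-group interaction; one prespecified baseline-adjusted contrast would say which format is better, when and by how much.

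*Protocol article*

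**What the plan says.** The Statistical analysis section states the tested effect as the "time (pre-intervention vs post-intervention vs follow-up 1 and 2 assessments) x group interaction", applied alike to the primary and secondary outcomes. On the model it says: "It will be examined with analysis of variance (ANOVA) mixed model for repeated measures when normal distribution will be detected". On where the groups differ it adds only: "A post hoc test will be used to locate the differences between the groups, if necessary". The level is set by "The significance level will be 0.05 for all statistical analyses". No covariate is named. The one multiplicity correction stated belongs to the Wilcoxon tests in the non-normal branch.

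FSS is the primary outcome. With the other questionnaires it "will be measured at pre-intervention, post-intervention and at three- and six-months follow-up". Neither the Abstract nor the outcome sections rank one of these visits first. The Discussion states the aim as whether fatigue improves, "if these changes are maintained in the short (3 months) and medium term (6 months) and compare it with traditional home rehabilitation using a booklet".

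Baseline FSS is measured before allocation. It is an entry criterion (4 points or more), and the Procedure section uses it to set the "starting level of the program which will depend on the pre-intervention FSS score".

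**The concern.** The trial compares two delivery formats of the same programme, so the reader needs a difference in FSS between the formats, with a sign, a visit and an interval. The planned primary test supplies none of these. It rejects when the two four-visit profiles are not parallel, whatever the pattern. That could mean a benefit of the platform at 12 weeks, a benefit of the booklet at six months, or a crossing of the two.

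The informative step is then a post hoc test with no named procedure, visit or adjustment. With three post-baseline visits and no primary one, the visit that is emphasised can be chosen after the data are seen.

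Treating baseline as a further outcome level also wastes information. Randomisation makes the expected baseline difference zero, so chance imbalance at that visit enters the comparison as noise, when it could be used to reduce residual variance.

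**Working it through.** **The plan's own figure.** The Sample size calculation section gives 20 + 20 + 10 = 50, an allowance of 10/50 = 20% for losses. This reproduces. It rests on pilot-study recommendations, so there is no power, effect size, SD or correlation to check.

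**Inputs from the document.** n = 20 per arm after losses; 1:1 allocation; level 0.05; four FSS visits; two groups.

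**Assumed, because the document gives none.** Two-sided testing; equal correlation ρ between any two visits; effects of 0.5 or 0.8 SD; the shape of the effect over time. Restricting entry to FSS of 4 or more may lower ρ, so a range is shown.

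**Formulas** (noncentral F, d in SD units, baseline difference 0):

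- Interaction: df = 3 and 3(2n − 2) = 114; λ = (n/2) Σ(d_t − mean d)² / (1 − ρ), summed over all four visits.
- Week-12 ANCOVA: df = 1 and 2n − 3 = 37; λ = (n/2) d² / (1 − ρ²).
- ANCOVA on the mean of the three post-baseline visits: df = 1 and 37; λ = (n/2) d̄² / [(1 + 2ρ)/3 − ρ²].

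**Worked case: constant 0.5 SD, ρ = 0.5.**

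- Interaction: effects (0, 0.5, 0.5, 0.5), mean 0.375, sum of squares 0.1875; λ = 10 × 0.1875/0.5 = 3.75; power 33%.
- Week 12: λ = 10 × 0.25/0.75 = 3.33; power 43%.
- Mean: variance term 2/3 − 1/4 = 0.417; λ = 10 × 0.25/0.417 = 6.0; power about 66%.

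**Correlation range, constant 0.5 SD (interaction vs week 12):** 24% vs 37% at ρ = 0.3; 33% vs 43% at 0.5; 52% vs 58% at 0.7; 71% vs 73% at 0.8; 96% vs 94% at 0.9. The week-12 advantage ends at ρ of about 0.83 for 0.5 SD and about 0.73 for 0.8 SD.

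**Shape of effect, 0.8 SD maximum, ρ = 0.5:**

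| Effect at 12 weeks, +3, +6 months | Interaction | Week 12 | Mean |
|---|---|---|---|
| Fading: 0.8, 0.4, 0.2 | 57% | 81% | about 60% |
| Growing: 0.4, 0.6, 0.8 | 57% | 30% | 82% |
| Late: 0, 0.4, 0.8 | 68% | 5% | 48% |

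A simulation (4000 runs, 0.8 SD) gave 74% for the interaction and 81% for week 12 with a constant effect at ρ = 0.5, and 68% against 5% with a late effect, in line with the formulas.

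**What does not depend on shape.** For any one visit, the residual variance is 1 unadjusted, 2(1 − ρ) for change from baseline, and 1 − ρ² with baseline as covariate. At ρ = 0.5 these are 1, 1 and 0.75. The adjusted figure is never larger than the other two, and it costs one degree of freedom.

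**The case against.** The strongest reply is that the interaction suits the stated aim. The Discussion asks about improvement, its maintenance at three and six months, and the comparison with the booklet. An interaction across those visits is a conventional and valid test of that under randomisation, and a week-12 contrast alone would answer only part of it. This stands. A reader might infer from the 12-week programme that week 12 is the trial's primary time point, but the document never says so.

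A reader might also infer that a baseline-adjusted week-12 test is simply more powerful. It is not in general. The ranking depends on a correlation and a time course that the document does not give, and it reverses when the effect builds after week 12. Power is also not what a pilot sized by recommendation should be judged on, and the Discussion itself expects no significant difference between formats.

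Third, the post hoc step reads as following a significant interaction, so there is some gating, and between-group effect sizes are planned for the main outcomes. That limits the freedom to choose a visit but does not remove it. Passing a 3-df test still leaves three visits open, and the effect sizes have no stated visit or adjustment.

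Finally, covariates and contrast order are often left to an analysis plan that is not shown. That would answer a complaint about silence. It does not answer this one, because the interaction is the method the protocol states.

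**Conclusion.** The point holds on interpretability. As written, the test of the primary outcome yields no direction, visit or estimate, and leaves the choice among three post-baseline visits to an unspecified later step. Feasibility is the secondary aim and efficacy on fatigue the main one, so pilot status makes a clear estimate with an interval more useful, not less.

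The power gain is conditional and secondary. For a constant 0.5 SD effect at correlation 0.5 and 20 per arm, it is 10 points for week 12 (33% to 43%) and about 33 points for the post-baseline mean (33% to about 66%). It can be zero or negative under other assumptions, and the documents give no basis for choosing among them. The benefit of adjusting a given visit's contrast for baseline FSS does not depend on the time course. The change is worth making before analysis; it does not invalidate the trial.

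**What to change.** In Statistical analysis, replace the omnibus interaction and its post hoc test as the primary criterion with one between-group difference in FSS, adjusted for baseline FSS and reported with a 95% CI. State in advance which contrast it is:

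- the end of the 12-week intervention, if the immediate effect of the programme is the question; or
- the mean of the three post-baseline visits, if the sustained effect is.

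Report the remaining visits, including three and six months for maintenance, as secondary contrasts from the same model, for example a mixed model with baseline FSS as covariate and the post-baseline visits as outcomes. The interaction may stay as a supporting test of whether the difference changes over time.

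The cost is a change of wording. Baseline FSS is already collected from every participant, and no visit or measurement is added. The downside is that a single contrast is less sensitive to patterns it does not target, such as a purely late effect, so the choice should be justified in a sentence.

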The use of telerehabilitation, defined as the delivery of rehabilitation services via technologies, appears to be a viable option [4, 13]. Furthermore, it could reduce the possible consequences of disease and prevent disability without the need to attend in person [12, 14, 19]. In addition, asynchronous telerehabilitation allows to incorporate home-based rehabilitation for the treatment of patients who have been discharged and do not require face-to-face treatment. This benefits especially to different population groups such as those who live in rural areas and has less access to health services, who experience any mobility limitations or have to be confined at their homes [20, 21].

According to the current scientific evidence, the efficacy of telerehabilitation has been demonstrated in many other pathologies such as the cardiac, neurological, respiratory, and musculoskeletal [19, 22–26]. There is already evidence of the efficacy of telerehabilitation interventions in the acute phase of COVID-19, at hospital setting patients and at home setting patients without hospitalization [27–30]. On the other hand, several studies have shown that telerehabilitation interventions can lead to an increased patient adherence and satisfaction [24, 31, 32]. To the authors’ knowledge, no previous studies have assessed if an asynchronous telerehabilitation program consisting of a combined therapeutic exercise and education program is effective to improve the functional status and the patient´s adherence and satisfaction of post-COVID-19 patients.

Therefore, the aim of this pilot study will be to analyze the efficacy on fatigue, functional status and psychosocial factors of a 12-weeks therapeutic exercise and education program, when this is delivered through an asynchronous telerehabilitation format versus a booklet-based rehabilitation format in post-COVID-19 patients.

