#### Eligibility criteria

All potential participants will be informed before and will have to give their consent to participate in the study. The inclusion criteria will be: 1) post-COVID-19 patients discharged after more than 5 days hospitalized; 2) aged 18 to 75 years; 3) independent standing with or without technical aids; and 4) present a degree of fatigue ≥4 points in the FSS. The exclusion criteria will be: 1) having any other central and/or peripheral neurological disorders; 2) a previous history of rheumatic pathology or acute musculoskeletal injury; 3) patients with severe hypoxemia, defined as having a SaO2 less than 90% or a respiratory rate ≥30; 4) having any cardiac comorbidities or signs of cardiovascular instability as uncontrolled arrythmia, blood pressure and/or effort angina; 5) having any other contraindicated pathology for moderate-intensity aerobic or strength exercise; 6) a score ≤24 evaluated with the validated Spanish version of Mini-mental State Examination (MMSE-MEC) [33]; 7) no access to internet; and 8) to be unable to follow oral and written instructions in the Spanish language.

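### If FSS or another questionnaire score is judged non-normal, the plan swaps the time-by-group analysis for Friedman and paired Wilcoxon tests, and no between-arm test remains

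*Protocol article*

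**What the plan says.** The Introduction sets a comparison of two delivery formats: the effect of the programme "when this is delivered through an asynchronous telerehabilitation format versus a booklet-based rehabilitation format in post-COVID-19 patients". On the endpoint, the protocol says: "The primary outcome measure will be the fatigue, measured with the Fatigue Severity Scale (FSS)".

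The Statistical analysis section gives the test of that comparison: "General lineal models will be performed to compare the intervention effects [time (pre-intervention vs post-intervention vs follow-up 1 and 2 assessments) x group interaction]", examined by mixed-model ANOVA when normality is found. The gate is stated in one sentence: "The Shapiro-Wilk test will be used to determine the normality of the data". For the case where the gate fails, the section says: "If data are not normally distributed, statistical analysis will be performed using non-parametric correspondent tests like Friedman test to compare the three moments involved". Wilcoxon tests follow if Friedman is significant, with the Wilcoxon type I error divided by the number of tests.

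A separate paragraph names between-group t-tests or Mann-Whitney tests for aerobic capacity, strength, post-COVID functional status and feasibility. Mann-Whitney appears once more, for baseline comparability. Between-group and within-group effect sizes (Cohen's d or r) are planned for the main outcomes.

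**The concern.** The fallback is presented as the non-parametric counterpart of the interaction model, but it answers a different question. Friedman and the paired Wilcoxon test ask whether scores change over time in the same patients. The interaction asks whether they change differently in the two arms. A reader who follows the text exactly would, on the non-normal branch, have p-values for change over time in FSS and none for telerehabilitation against booklet.

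Both arms receive the same exercise and education programme, and patients are enrolled soon after hospital discharge. Improvement over time is therefore likely in both arms, and a significant Friedman test would say nothing about delivery format. Whether the primary outcome gets a between-arm test would be decided by a preliminary test on the data.

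**Working it through.** **1. Which outcomes have a between-arm test on each branch (Statistical analysis section).**

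| Outcome | Normal data | Non-normal data |
|---|---|---|
| FSS (primary), GSES-12, DASS-21, SF-12, BRSQ-36, MSPSS | time-by-group mixed ANOVA | Friedman, then Wilcoxon: none between arms |
| 6MWT, STST, ACT, PCFS, feasibility | independent t-test | Mann-Whitney |
| Baseline comparability | t-test | Mann-Whitney |

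Wilcoxon must mean the paired signed-rank test here. It follows Friedman as the pairwise step, and the two-sample rank test is named separately as Mann-Whitney.

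**2. Friedman carries no information on arm.** With n patients and k visits the statistic is 12/(nk(k+1)) × ΣRj² − 3n(k+1), where Rj is the sum over patients of the within-patient ranks at visit j. Arm does not appear. As a check, moving 40 simulated patients at random between arms left the pooled statistic at 1.71 both times. This needs no distributional assumption. Running Friedman separately in each arm gives two within-arm verdicts and still no comparison.

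**3. Number of visits.** The Outcome measures section schedules these questionnaires pre-intervention, post-intervention and at three and six months: four assessments. The ANOVA sentence also lists four. The fallback sentence says three.

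**4. Sample size.** The plan's figure reproduces: 2 × 20 + 10 = 50. So 20 per arm is the number after losses and 25 per arm the number recruited. No effect size, SD or power is given, so everything below rests on assumptions.

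**5. What the fallback does and does not detect.** Assumptions: baseline FSS normal with mean 5.2 and SD 1.1, truncated to 4–7 and rounded to ninths (nine items); change with a patient part and a visit part, each SD 0.63; four visits; 20 per arm; 1,000 runs; two-sided 0.05.

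| True improvement, arm A / arm B (points) | Friedman significant in both arms | In exactly one arm | Mann-Whitney on change to post-intervention |
|---|---|---|---|
| 0 / 0 | 0.3% | 9.9% | 4.5% |
| 0.5 / 0.5 | 36% | 47% | 6.0% |
| 1 / 1 | 99% | 0.9% | 3.9% |
| 1.5 / 0.7 | 89% | 11% | 75% |
| 1.5 / 0.5 | 60% | 40% | 92% |

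The first three rows have no arm difference; the last two do.

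**6. Discordant within-arm Wilcoxon verdicts when both arms improve equally.** If each arm is significant with probability p, exactly one is significant with probability 2p(1−p), which peaks at 50% when p = 0.5. With 20 per arm and normally distributed changes, simulated:

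| Equal change (SD of change) | alpha 0.05 | alpha 0.05/6 (six visit pairs) |
|---|---|---|
| 0 | 9% | 2% |
| 0.2 | 22% | 7% |
| 0.5 | 50% | 39% |
| 0.8 | 16% | 41% |
| 1.0 | 3% | 16% |
| 1.2 | under 1% | 3% |

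For example, at 0.5 SD and alpha 0.05, p is about 0.54: 2 × 0.54 × 0.46 = 0.50.

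**7. How likely the branch is.** Eligibility requires patients to "present a degree of fatigue ≥4 points in the FSS", on items scored 1 to 7, so baseline FSS lies between 4 and 7. For an underlying mean of 4.5 to 5.5 and SD of 1.1 to 1.2, Shapiro-Wilk on truncated, rounded baseline FSS rejects in about 8–21% of runs with 20 patients, 21–57% with 40 and 33–69% with 50. The section does not say whether the test is applied to scores, changes or residuals, or per arm or pooled, so no single probability follows.

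**The case against.** Several points on the other side are fair.

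- **A reader might infer that any normality failure removes the trial's question.** The text does not support that. The performance tests, PCFS and feasibility outcomes keep Mann-Whitney between arms. The Discussion also asks whether fatigue improves and whether the gain lasts to three and six months; Friedman and Wilcoxon can address that part.
- **A between-group effect size is planned.** So within-arm verdicts are not the only thing a reader would have. This stands and narrows the gap. It is an estimate with no named test, however, and the section says nothing of an interval around it.
- **Friedman is introduced as an example, and an article condenses a fuller plan.** That leaves some latitude. But the tests that are named are called the counterparts of the interaction model, and they are not. That is a wrong statement, not an omitted detail.
- **A reader might infer that the authors will claim an arm difference when only one arm is significant.** Nowhere does the plan say so. The discordance figures show what would happen if someone did, and a figure near 50% is the ceiling of 2p(1−p), reached only around one effect size.
- **A reader might assume eight Shapiro-Wilk tests (two arms, four visits), any one of which triggers the switch.** That would give 1 − 0.95^8 = 34% even for perfectly normal, independent data, but neither the number of tests nor the rule is in the document.
- **This is a pilot.** True, and the gap is conditional. Yet the stated aim is efficacy, and 0.05 is set for all analyses.

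**Conclusion.** Wrong as written, for the primary outcome and the five other questionnaires, on the non-normal branch only. That the named tests ignore arm follows from their definition and rests on no assumption. The size of the harm does rest on assumptions. Under those shown, the branch would be entered in anywhere from under a tenth to about two thirds of trials if baseline FSS is what gets tested. Reading within-arm verdicts as an arm comparison would produce discordance under equal benefit in about 0 to 50% of trials. It could also hide a real difference: with 1.5 against 0.7 points, both arms are significant in 89% of runs. A rank test between arms under the same assumptions rejected in 3.9% to 6.0% of runs with no difference, and in 75% to 92% with the two differences tried.

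**What to change.** State one between-arm analysis for FSS, GSES-12, DASS-21, SF-12, BRSQ-36 and MSPSS that applies whatever Shapiro-Wilk shows. Either of these would do:

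- at minimum, when data are non-normal, a Mann-Whitney test (or rank ANCOVA) between arms on change from baseline at each post-baseline visit; or
- a baseline-adjusted mixed model with robust or bootstrap intervals throughout, which makes the normality switch unnecessary.

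If the switch is kept, say what Shapiro-Wilk is applied to and which result triggers it. Label Friedman and Wilcoxon as within-arm description only, and change three time points to the four in the Outcome measures section. The cost is rewording one paragraph before the data are analysed; no extra patients, visits or data are needed.

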#### Secondary outcomes: Functional status, psychosocial factors, quality of live and feasibility

*Functional status*. It will be measured using the main recommended test for post-COVID-19 patients [46].

Aerobic capacity
6MWT is a sub-maximal exercise test used and recommended to assess the maximum distance possible for six minutes, in a 30-meter corridor, allowing the patient to rest as needed. It has been shown to be reliable [47–49]. The distance covered by each participant will be compared with the estimated distance for their gender, weight, and age according to the Troosters equation [50–52].Strength
30” STST is part of the Senior Fitness Test (SFT) designed by Rikli and Jones and it will be used as a stand-alone test, especially to assess weakness in respiratory patients who have passed COVID-19 [53–55]. It has been shown to be reliable in adults with asthma or pulmonary hypertension [53, 56–58]. This test will be performed with a chair, with the patient´s feet resting on the floor and the arms crossed on the chest. Once in this position, the patients will sit down and stand up to the starting position as many times as possible within 30 seconds [59].30” ACT is part of the SFT and is also used as a stand-alone test to assess strength. It has been shown to be reliable [53, 60, 61] in deconditioned patients and in the elderly population. From a sitting position, the patient is asked to do as many elbow flexion-extension movements as possible with his/her dominant limb during 30 seconds with a two kg weight. The higher number of repetitions the better strength [53, 59].Functional Status post-COVID
PCFS is a scale specially designed and that has been shown to be reliable to assess the functional status of patients who have gone through COVID-19 at discharge [50, 62–64]. It consists of four levels of post-COVID-19 functional limitations been: D = death; 0 = no limitation; 1 = no significant functional limitation; 2 = mild functional limitation; 3 = moderate functional limitation; 4 = severe functional limitation. This scale can be administered by telephone or self-administered [12].

*Psychosocial factors*.

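### Functional outcomes are given two analyses with no order of precedence; three of them lack the visits for the four-visit model, and the two-sample alternative names no baseline adjustment

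*Protocol article*

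**What the plan says.** Three statements in the protocol article bear on this.

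- **The model.** Under Statistical analysis, general linear models examine "time (pre-intervention vs post-intervention vs follow-up 1 and 2 assessments) x group interaction". The list of variables analysed this way opens with the words "on the primary and secondary outcomes: severity of fatigue, functional status, self-efficacy, depression, anxiety and stress, quality of live"; further scales follow. Functional status is thus on that list.
- **The two-sample test.** Later in the same section: "For the aerobic capacity, strength, functional status post-COVID and feasibility outcomes, comparisons between-groups outcomes will be using t-tests for independent samples". Mann-Whitney is the non-parametric alternative, and chi-square or Fisher tests are named for categorical data.
- **The visits.** Under Secondary outcomes: "The functional status outcomes (6MWT, 30” ACT and 30” STST) only will be measured pre- and post-intervention". PCFS is in a separate list of outcomes that "will be measured at pre-intervention, post-intervention and at three- and six-months follow-up".

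The Secondary outcomes section uses functional status as the heading over four measures: 6MWT (aerobic capacity), STST and ACT (strength), and PCFS, whose sub-heading is Functional Status post-COVID. PCFS is a graded scale, starting "D = death; 0 = no limitation; 1 = no significant functional limitation" and running to 4. The article does not say which analysis governs, whether the t-test is on post-intervention values or on change, or which visit it uses for PCFS. It gives no pre-post correlation.

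**The concern.** Functional status is part of the trial's stated aim, and its measures are named under two methods that answer different questions, each at the 0.05 level. With no order of precedence, the choice of analysis stays open until the data are seen. For PCFS the choice of visit stays open too.

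For the three performance tests, one of the two analyses does not match the data that will exist. The other, as written, mentions neither a covariate nor a change score. In a trial planned for 20 patients per arm, the baseline value is the cheapest source of precision, and it also removes the effect of chance baseline imbalance from the estimate. In the plan, baseline values otherwise serve only a comparability test between the groups, and no consequence for the analysis follows from it.

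**Working it through.** **Step 1. Which outcome has which analysis?** The term functional status is used in two ways, so I checked each possible meaning in the model list.

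| Meaning of functional status in the model list | 6MWT, STST, ACT (2 visits) | PCFS (4 visits) |
|---|---|---|
| All four measures (the section heading) | Two analyses; four-level model cannot be fitted | Two analyses; no visit named for the two-sample test |
| The three performance tests (the visit paragraph) | Two analyses; four-level model cannot be fitted | Two-sample test only, visit not named |
| PCFS only | Two-sample test only | Two analyses; no visit named for the two-sample test |

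No reading leaves every outcome with a single, fully stated analysis. The non-parametric fallback does not resolve this: it refers to three time points, which matches neither two visits nor four.

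**Step 2. The plan's own figure.** Sample size calculation: 2 x 20 + 10 = 50, which is also 40/(1 - 0.20) = 50. The figure reproduces. No power, effect size or SD is given, so there is no power statement to check.

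**Step 3. What baseline adjustment is worth for 6MWT, STST and ACT.** Inputs: n = 20 per arm after losses (Sample size calculation), 1:1 allocation (Allocation and blinding), and alpha 0.05 (Statistical analysis), taken as two-sided because sidedness is not stated. The pre-post correlation rho is my assumption, with a main range of 0.5 to 0.8. Variances are taken as equal before and after treatment.

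Variance of the group difference, relative to a t-test on post-intervention values:

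- post-only t-test: 1
- t-test on change: 2(1 - rho)
- ANCOVA: 1 - rho^2

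Information lost against ANCOVA is rho^2 for the post-only test. For the change test it is 1 - (1 - rho^2)/[2(1 - rho)] = (1 - rho)/2.

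95% CI half-width in SD units: post-only 2.024 x sqrt(2/20) = 0.64; change 0.64 x sqrt(2(1 - rho)); ANCOVA 2.026 x sqrt(2/20) x sqrt(1 - rho^2).

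| rho (assumed) | Loss, post-only | Loss, change | Half-width: post-only | change | ANCOVA |
|---|---|---|---|---|---|
| 0.5 | 25% | 25% | 0.64 | 0.64 | 0.55 |
| 0.7 | 49% | 15% | 0.64 | 0.50 | 0.46 |
| 0.8 | 64% | 10% | 0.64 | 0.40 | 0.38 |

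Over a wider range, rho 0.3 to 0.9, the post-only loss runs from 9% to 81% and the change-score loss from 35% down to 5%.

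**Step 4. What ANCOVA costs.** It uses one degree of freedom (37 instead of 38). Estimating the slope inflates the variance by roughly 1/(2n - 4) = 1/36, about 3%. Allowing for that, the post-only losses become 22.9%, 47.6% and 63.0% at rho 0.5, 0.7 and 0.8.

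**The case against.** The best reply is that the second sentence is the specific rule: it names aerobic capacity and strength because those outcomes have no follow-up visits. With two visits, moreover, the time x group interaction of a mixed ANOVA is algebraically the independent t-test on change (F = t^2). If the t-test is on change and time is cut to two levels, the two analyses coincide. This stands as mathematics. But the plan writes four levels, does not say the test is on change, and does not say that the later sentence overrides the earlier one.

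It is also fair that an unadjusted two-sample test is valid under randomisation, that Mann-Whitney is a legitimate test for an ordinal grade, that these are secondary outcomes of a pilot and feasibility study, and that a condensed article leaves detail elsewhere. The first three points limit the weight of the finding. The last does not remove it, because the article fixes methods by name for named outcomes and those statements conflict.

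Three stronger readings are tempting and not supported.

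- A reader might infer that the plan discards baseline. A post-value comparison is the more natural reading, but a change-score test is not excluded.
- A reader might infer that about half the precision is lost. That needs post-only values, an assumed rho near 0.7, and precision read as variance. At that rho the CI half-width falls only from 0.64 to 0.46 SD, that is 28%.
- A reader might infer that all functional outcomes lack the follow-up visits. PCFS has all four.

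**Conclusion.** The point holds as an inconsistency of assignment. Taking functional status as the section heading defines it, all four measures carry two analyses with no precedence. The four-visit model cannot be fitted to 6MWT, STST and ACT. PCFS is doubly assigned, with no visit stated for its two-sample test.

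For the three performance tests, ANCOVA improves on either form of t-test across the assumed range. The gain is 25-64% of the information against post-only values (half-width 0.64 down to 0.55-0.38 SD) and 25-10% against change, for rho 0.5 to 0.8. These sizes rest on an assumed correlation, equal variances and 20 evaluable patients per arm; the article supplies only the last. The correction should be made, but it concerns secondary outcomes and does not touch the validity of the randomised comparison.

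**What to change.** Give each outcome one analysis that matches its visits.

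- **6MWT, STST and ACT:** take them out of the four-visit model. Use ANCOVA of the post-intervention value on group and the pre-intervention value.
- **PCFS:** name one governing analysis that suits an ordinal grade and uses its repeated visits and baseline. State the visit of main interest and how the non-numeric death grade is coded. PCFS should not be removed from longitudinal analysis. With about 20 patients per arm some grades may be sparse, so the model should be simple and a fallback stated.
- **Feasibility outcomes without a baseline:** keep the t-test or Mann-Whitney test.
- **Terminology:** use functional status in one sense throughout, or list the measures by name.

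The cost is a change of wording and one degree of freedom per ANCOVA. Every variable needed is already collected, and no visit or patient is added.
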